## Abstract

**Background:**

Geohelminth infections are highly prevalent infectious diseases of childhood in many regions of the Tropics, and are associated with significant morbidity especially among pre-school and school-age children. There is growing concern that geohelminth infections, particularly exposures occurring during early life *in utero *through maternal infections or during infancy, may affect vaccine immunogenicity in populations among whom these infections are endemic. Further, the low prevalence of allergic disease in the rural Tropics has been attributed to the immune modulatory effects of these infections and there is concern that widespread use of anthelmintic treatment in high-risk groups may be associated with an increase in the prevalence of allergic diseases. Because the most widely used vaccines are administered during the first year of life and the antecedents of allergic disease are considered to occur in early childhood, the present study has been designed to investigate the impact of early exposures to geohelminths on the development of protective immunity to vaccines, allergic sensitization, and allergic disease.

**Methods/Design:**

A cohort of 2,403 neonates followed up to 8 years of age. Primary exposures are infections with geohelminth parasites during the last trimester of pregnancy and the first 2 years of life. Primary study outcomes are the development of protective immunity to common childhood vaccines (i.e. rotavirus, *Haemophilus influenzae *type B, Hepatitis B, tetanus toxoid, and oral poliovirus type 3) during the first 5 years of life, the development of eczema by 3 years of age, the development of allergen skin test reactivity at 5 years of age, and the development of asthma at 5 and 8 years of age. Potential immunological mechanisms by which geohelminth infections may affect the study outcomes will be investigated also.

**Discussion:**

The study will provide information on the potential effects of early exposures to geohelminths (during pregnancy and the first 2 years of life) on the development of vaccine immunity and allergy. The data will inform an ongoing debate of potential effects of geohelminths on child health and will contribute to policy decisions on new interventions designed to improve vaccine immunogenicity and protect against the development of allergic diseases.

**Trial registration:**

Current Controlled Trials ISRCTN41239086.

## Background

The geohelminth (also known as intestinal or soil-transmitted helminth infections) parasites, *Ascaris lumbricoides, Trichuris trichiura*, hookworm, and *Stronglyoides stercoralis*, are common infectious diseases of childhood in tropical regions and are estimated to infect over 2 billion humans worldwide [1]. Geohelminth infections are considered to cause significant morbidity in endemic areas through affects on nutrition, growth, and cognition affecting school performance [2].

Geohelminth infections induce an immune responses in humans characterized by elevated IgE levels, eosinophilia, and increased production of Th2 cytokines from peripheral blood leukocytes in response to stimulation by parasite antigen [3]. While initial exposures to these parasites may be associated with enhanced allergic inflammatory responses to the parasite, in long-term infections and with repeated exposures, the host inflammatory response becomes more tightly controlled [4,5]. Chronic infections have potent regulatory effects on anti-parasite inflammatory responses [5,6], being associated with a modulated or 'modified' Th2 responses that may facilitate parasite survival but protect the host from damaging immune-mediated disease [4]. The regulation of host immunity by chronic geohelminth infections may not just affect responses to parasite antigens but also other exogenous antigens such as the antigenic constituents of vaccines and aeroallergens. Such effects may contribute to the impaired vaccine immunogenicity [7-10] and decreased prevalence of allergic diseases [5,11] reported from the rural Tropics.

The prevalence of allergic diseases has increased over the past 40 years and has reached epidemic levels in many developed countries such as the UK, [12] where they are now the most prevalent chronic diseases of childhood. International surveys showed that the prevalence of asthma varied 20-fold between countries, ranging 1.6-36.8% [13], and a surprising finding was the high prevalence of asthma in urban centres in Latin America with prevalence rates as high as those reported from traditional high prevalence countries [13,14].

The causes of the high prevalence of allergic diseases in developed countries and the increasing prevalence in many developing countries are not known. The most widely accepted explanation is the 'hygiene hypothesis' that has attributed the increases in prevalence to a decline in infectious and microbial exposures during childhood [12,15,16]. This was initially explained in the context of the effects of early infectious exposures on the Th1/Th2 cytokine balance: a greater infectious burden induces stronger Th1 responses that counterbalanced the effects of pro-allergic Th2 responses. The observation that chronic helminth infections, that induce strong Th2 immunity, appeared to protect against allergy stimulated a re-working of the hypothesis to emphasize the role of immune regulatory mechanisms to control Th1 and Th2-mediated inflammation [17,18]. Current thinking has emphasized the importance of multiple early infectious exposures including helminths in the induction of an immune regulatory network [6,11,19] that controls inflammatory responses to both Th1 and Th2-inducing stimuli. Important mediators of immune regulation may include subsets of regulatory immune cells [4,20-23].

There is evidence from experimental animal models that intestinal and tissue helminth infections have deleterious effects on vaccine immune responses [24,25]. Further, intestinal helminth infections have been shown to either enhance [26,27] or suppress [27-29] allergic inflammatory responses in different experimental models of allergic inflammation. Studies conducted in children and adults indicate that concurrent geohelminth infections can suppress protective immune responses to both parenteral [30,31] and oral [32] vaccines and are inversely associated with the prevalence of allergen skin test reactivity [5,33] used as a marker for atopy or allergic sensitization. Geohelminth infections have also been associated with either a reduced [34] or increased prevalence [5,34] of asthma depending on the prevalence and type of geohelminth parasite present.

Because the antecedents of allergic diseases are considered to occur in early life and most vaccines are administered during the first year of life before geohelminth infections are acquired, there is interest in the potential effects of maternal geohelminth infections on infant morbidity [35], and the effects of such exposures on vaccine immune responses during infancy [31,35-37] and the development of allergic sensitization and allergic diseases [5,35,38,39]. There is evidence that maternal helminth infections bias the fetal immune response [31] an effect that persists into infancy and that may interfere with protective immunity associated with vaccines such as BCG [40]. Similarly, maternal ascariasis is associated with sensitization to *A. lumbricoides *antigens in newborns [41], although the long-term consequences of such sensitization are unclear.

The present study is investigating the potential effects of intrauterine and postnatal exposures to geohelminths on vaccine immune responses in infancy, and the development of allergic sensitization and allergic inflammatory diseases in childhood. The study will also investigate the immunological mechanisms by which such effects occur. The findings of this study have clear policy implications given that anthelmintic treatment of school-age children for the control of geohelminth infections is now a widely implemented public health strategy [42,43], and the use of anthelmintic treatment during pregnancy has been advocated to improve the health of mothers and infants [43,44]. Few opportunities, therefore, still exist to study the development of allergic disease in early childhood in the context of endemic geohelminth infections.

### Hypotheses

This study has been designed to investigate four specific hypotheses relating to the effect of maternal and infant infections with geohelminths on host immune responses and development of allergic inflammatory diseases: 1) chronic exposures to geohelminth infections (i.e. maternal geohelminth infections and infant geohelminth infections within the first 2 years of life) suppress immune responses to childhood vaccines; 2) chronic exposures to geohelminth infections suppress aeroallergen skin test reactivity; 3) chronic exposures to geohelminth infections protects against the development of eczema; and 4) chronic exposures to geohelminth infections protect against the development of asthma but non-chronic exposures (i.e. later childhood exposures occurring after 2 years in the absence of maternal geohelminth infections) increase the risk of asthma.

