### Study power

The study sample size is fixed at 2,403 newborns. Primary outcome variables will be treated as statistically independent. Power calculations for primary study questions are shown in Table 2[58,59]. We expect a high degree of power for the estimation of most primary and secondary study outcomes (≥ 80% depending on immunological mechanism at α = 0.01) that will allow for the loss of power expected by controlling for confounding.

**Table 2 T2:** Power for analysis of primary exposure-outcome associations

Primary exposures (geohelminth infections)	Outcome	Sample size available	Analysis sample size	Exposure prevalence	Expected prevalence of outcomes (exposed vs. unexposed groups)	Α	Power
Maternal	Vaccine antibodies @ 7 mths						
	Hib	2,300	1,000	50%	65% vs. 75%	0.01	80%
	Rotavirus	2,300	1,000	50%	40% vs. 60%	0.01	> 99%
Maternal	Vaccine antibodies @ 2 yrs						
	TT	1,955	1,000	50%	85% vs. 95%	0.01	> 99%
	HBV	1,955	1,750	50%	80% vs. 85%	0.05	80%
	OPV type 3	1,955	500	50%	80% vs. 95%	0.01	> 99%
Infant	Vaccine antibodies @ 5 yrs						
	TT	1,725	1,000	35%	60% vs. 80%	0.01	99%
	HBV	1,725	1,500	35%	70% vs. 80%	0.01	95%
	OPV type 3	1,725	1,000	35%	50% vs. 70%	0.01	> 99%

Maternal	SPT @ 3 years	1,840	1,840	50%	15% vs. 25%	0.01	99%
Infant	SPT @ 3 years	1,840	1,840	35%	15% vs. 25%	0.01	> 99%

Maternal	Eczema @ 3 years	1,840	1,840	50%	25% vs. 35%	0.01	99%

Maternal	Asthma @ 5 years	1,725	1,725	50%	17% vs. 23% #	0.05	86%
Infant	Asthma @ 5 years	1,725	1,725	35%	17% vs. 23% #	0.05	83%
Infant	Asthma @ 5 years	1,725	1,207	20%	25% vs. 15% #	0.01	93%

Random samples of the study population will be selected for analysis of the protective levels of vaccine antibodies. Based on data from the cohort we estimate that 20% of children will have allergen skin test reactivity to any allergen at 5 years, that 30% of children will have at least one documented episode of eczema by 3 years of age and that 20% of children will have asthma at 5 years. Based on data from the cohort we estimate that ~50% of mothers are infected with any geohelminth parasite and ~30% of children will have at least one documented geohelminth infection during the first 2 years of life.

#-expected effects of geohelminth infections on asthma prevalence using data from cross-sectional analyses in Ecuador [58] and Brazil [59].

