**Figure 4 F4:**
[figure not shown]
**Conceptual model for the effects of maternal and infant geohelminth infections on asthma in children**. The effects of these exposures on asthma are considered to occur via effects on bronchial hyperreactivity. The protective effects of chronic helminth exposures (maternal and infant infections within the first 2 years of life) are presumed to occur via the development of a modified Th2 (mTh2) response that may affect bronchial hyperreactivity through: 1) Immune regulation/suppression-suppression of airways inflammation via enhanced production of geohelminth or aeroallergen-induced IL-10. 2) Homeostasis-enhanced production of spontaneous IL-10 will suppress airways inflammation non-specifically. Alternatively children without early geohelminth exposures and that are first exposed to infection after 2 years of age (> 24 m) may respond to *A. lumbricoides *infection with strong inflammatory responses in the airways that up-regulate pro-inflammatory pathways including Th1, Th2, and Th17. The modified Th2 response will be defined by the presence of specific IgG4 antibodies to geohelminths. RTIs- respiratory tract infections. ETS-environmental tobacco smoke.

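### Table 2 sizes the apparent late-infection asthma comparison at 1,207 children, but at most about 862 can meet hypothesis 4's no-maternal-infection condition, and the stated 93% power does not hold at the row's alpha

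*Protocol article*

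**What the plan says.** The Hypotheses section splits hypothesis 4 in two. Chronic exposure is expected to protect against asthma, and is described as "chronic exposures to geohelminth infections (i.e. maternal geohelminth infections and infant geohelminth infections within the first 2 years of life". Late exposure is expected to do harm: "non-chronic exposures (i.e. later childhood exposures occurring after 2 years in the absence of maternal geohelminth infections) increase the risk of asthma".

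The Figure 4 legend gives the same picture. Protection is attributed to early infection: "The protective effects of chronic helminth exposures (maternal and infant infections within the first 2 years of life". The harmful pathway is reserved for "children without early geohelminth exposures and that are first exposed to infection after 2 years of age".

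Table 2 (Study power) has three rows for asthma at 5 years. Two predict protection, 17% vs 23%, in all 1,725 children. The third predicts harm and reads "1,725 1,207 20% 25% vs. 15" per cent, with alpha 0.01 and power 93%. Its exposure label is *Infant*. The Table 2 footnote gives the prevalences: "we estimate that ~50% of mothers are infected with any geohelminth parasite", and about "30% of children will have at least one documented geohelminth infection during the first 2 years of life".

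**The concern.** The third asthma row is the only place where the late-infection half of hypothesis 4 seems to be sized. Its N does not fit the population that the hypothesis and Figure 4 describe. If 1,207 is taken at face value, the set must contain hundreds of children whose mothers were infected. Hypothesis 4 regards these children as exposed to something protective.

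Two things are at stake. The first is the power statement for one half of a primary hypothesis, because the qualifying set is much smaller than the one used. The second is the contrast itself: children of infected mothers in the late-infected group, the comparison group or both would bias the estimate, in a direction that depends on where they sit.

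**Working it through.** **Inputs.** From Table 2: 1,725 children available at 5 years; row N 1,207; 20% exposed; asthma 25% vs 15%; alpha 0.01; power 93%. From the Table 2 footnote: mothers infected about 50%; children infected in the first 2 years about 30%.

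**1. Where 1,207 comes from.** 1,725 × (1 − 0.30) = 1,207.5. The row removes the children infected before age 2 and no others. (The 35% used in the other *Infant* rows would give 1,725 × 0.65 = 1,121.)

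**2. How many can qualify.**
- Upper bound, uninfected mother: 1,725 × 0.50 = 862.5.
- So at least 1,207 − 862.5 = 344.5, about 345, of the 1,207 have infected mothers. With the 1,854 children that Study limitations expects at 5 years as the base, the minimum is 1,207 − 927 = 280.
- Neither exposure, if the two are independent (assumption): 1,725 × 0.50 × 0.70 = 604. About 603 of the 1,207 then have infected mothers.
- Neither exposure, if infant infection is RR times as likely with an infected mother (assumption): P(infant infection, mother uninfected) = 0.30 / (0.5 + 0.5 × RR). RR = 1.5 gives 0.24 and 862.5 × 0.76 = 656 children. RR = 3 gives 0.15 and 862.5 × 0.85 = 733.

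**3. The plan's own power figure.** Normal approximation for two proportions, with n1 = 0.20N, n2 = 0.80N and pooled rate p = 0.2 × 0.25 + 0.8 × 0.15 = 0.17:

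power = Φ[(0.10 − c − z × SE0) / SE1], where SE0 = √[p(1 − p)(1/n1 + 1/n2)], SE1 = √[0.25 × 0.75/n1 + 0.15 × 0.85/n2], and c is 0 or the continuity correction ½(1/n1 + 1/n2).

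For N = 1,207: n1 = 241.4, n2 = 965.6, SE0 = 0.02703, SE1 = 0.03015, correction = 0.00259.
- Alpha 0.01, no correction: (0.10 − 2.576 × 0.02703)/0.03015 = 1.008, power 84%. With correction: 82%.
- Alpha 0.05, with correction: (0.09741 − 1.960 × 0.02703)/0.03015 = 1.474, power 93.0%.

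The printed 93% is therefore the alpha 0.05 result. The same corrected formula gives 86.4% and 82.5% for the other two asthma rows, printed as 86% and 83% at alpha 0.05, which supports this reading.

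**4. Power in the restricted set.** Same formula, 25% vs 15%, 20% late-infected (assumed to carry over), two-sided; each cell shows with / without continuity correction.

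| N | alpha 0.01 | alpha 0.05 |
|---|---|---|
| 1,207 (as printed) | 82% / 84% | 93% / 94% |
| 862 (upper bound) | 65% / 69% | 83% / 85% |
| 604 (independence) | 47% / 51% | 68% / 72% |

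For 656 to 733 children, power at alpha 0.01 without correction is 55% to 61%.

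**The case against.** **The row does not say late infection.** This is true. The reading is inferred from three features: the reversed direction, the 20% exposure where the other infant rows have 35%, and an N equal to what remains after removing infection before age 2. The alternative is worse. Read literally, the table would predict both protection (17% vs 23%) and harm (25% vs 15%) for the same exposure and outcome. The section on geohelminth exposures also confines infant infection to the first 2 years. The label needs correcting on either reading.

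**A power row does not define an analysis set.** This also stands. The Analysis plan names maternal and infant infection as exposures and sets out no late-infection population; a fuller document may do so. A reader might infer that the planned analysis mixes the two kinds of children in both groups and so pulls the effect toward the null. The article does not establish that. The exposed group is 20% × 1,207 = 241 children, who could all have uninfected mothers. Then at least 345 children of infected mothers would sit in the comparison group. If they are protected, as hypothesis 4 expects, the comparison rate falls and the contrast moves away from the null.

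**The hypothesis text alone excludes only maternal infection.** Correct. The additional exclusion of early infant infection comes from the Figure 4 legend. On the narrower wording the ceiling is about 862, still well below 1,207.

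**The loss of power can be exaggerated.** Setting the printed 93% against about 50% would mix two separate faults, because the 93% belongs to alpha 0.05. Like for like at alpha 0.05 with correction, 93% falls to 68% at 604 and to 83% at 862.

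**Conclusion.** The point holds as a mismatch between the stated hypothesis and the figures in Table 2. On the document's own prevalences, 1,207 children cannot all have uninfected mothers: at least 345 do not, and about 603 do not under independence. The printed power is wrong for the hypothesis as defined, and it is also wrong for the row's own N and alpha. In the qualifying set no feasible size reaches 80% at alpha 0.01; at alpha 0.05 only sizes near the 862 ceiling do.

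The conclusion assumes that the row is the late-infection calculation and that the approximate 50% and 30% prevalences hold among children seen at 5 years. The power figures further assume that late infection stays at 20% in the restricted set, and the 604 assumes independence of maternal and infant infection. What is not supported is any claim about how the final analysis will be run, or a fixed direction of bias.

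**What to change.** Reconcile the Hypotheses section and the Figure 4 legend with the last asthma row of Table 2:

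- Relabel the exposure as late infection (first infection after 24 months).
- Define the set as children with no maternal third-trimester infection and no positive stool up to the 24-month visit, comparing first infection after 24 months with no infection.
- Restate N (about 600, at most 862), the assumed late-infection prevalence in that set, alpha and power, with alpha and power matching each other.
- If wanted, keep the 1,207-child set as a supporting analysis with a late-infection-by-maternal-infection interaction term.

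The maternal and serial child stool samples needed are already in the sampling schedule, so recruitment, measurement and follow-up do not change. The cost is one analysis-set definition, one restated row and a less favourable power figure for this question.

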## Methods/design

### Study design

The study is a birth cohort of 2,403 children recruited from around the time of birth in HPAB over the period November 2005 to December 2009. The recruitment area for the cohort is defined geographically by the boundaries of the District of Quinindé, Esmeraldas Province in Northern coastal Ecuador (Figure 1). The primary exposures are maternal and infant infections with geohelminths and the primary outcomes are vaccine immunity, atopy and allergic disease.

**Figure 1 F1:**
[figure not shown]
**Study site**. A. Map of Ecuador showing location of District of Quinindé, Esmeraldas Province (black oval) (Courtesy of The General Libraries, The University of Texas at Austin). The recruitment area for the cohort was defined by the geographic boundaries of this district. B. Map showing parishes the District of Quinindé including La Concordia. H-Hospital Padre Alberto Buffoni. C. Geographic location of households of cohort infants.

### Study population and area

The Province is one of the poorest regions of Ecuador, with a per capita income of less than US$2,000 in 2005. Quinindé is a rural District that covers an area of 3,471 km^2 ^and includes 1 urban (the town of Quinindé) and 6 rural parishes with an estimated population of 150,000. The District is located in an area of (formerly) equatorial rainforest that has largely been cleared, at an altitude of approximately 100 m and average annual day temperature of 30°C and 75% humidity. The District has an ethnically mixed population of mestizos (90%), Afro-Ecuadorians (7%), and Amerindians (3%). Twenty-two percent of the population is estimated to be urban (Quinindé town) and 78% rural. In the town of Quinindé, approximately 90% of the population have access to electricity, 60% to treated drinking water, 40% to sanitation; 60% to solid waste disposal services. In contrast, in the rural areas, 10% have access to electricity and none have access to other services. The main sources of income are derived from African palm oil and fruit cultivation, cattle, and extraction of timber. The study is based at the Hospital "Padre Alberto Buffoni" (HPAB) (H in Figure 1) in Quinindé town. HPAB is the only Hospital serving the District and the only health centre with maternity services.

### Inclusion criteria

Although assessments and sampling are conducted during pregnancy, only a proportion of pregnant mothers attend antenatal clinics, and formal recruitment into the cohort occurs around the time of birth. Entry criteria into the study are: 1) healthy normal baby less than 14 days old; 2) at least one stool sample collected from the mother; 3) the family has lived in the District for the last 2 years and does not plan to move out of the District over the following 3 years; 4) the home is accessible; and 5) the mother is 17 years or older.

